### Waiting list condition

The control condition includes a WLC. At 5 months after start (i.e., T4) participants in the WLC receive the opportunity to follow the intervention without email guidance by a therapist. They neither receive a welcome letter at the start, which means that they only read the introduction about the training before starting.

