#### Other outcomes

Qualitative data on intervention experiences and satisfaction will be collected by means of interviews with some participants after completion of the intervention. In this way, it will be possible to examine experiences, usage, usability, content fit of intervention with complaints, and satisfaction. Specifically, both participants who adhered and did not adhere to the intervention will be interviewed. Patients adhered to the intervention if all sessions were completed (i.e., based on data retrieved from Karify) and a minimum of 2 h per week was spent on the intervention (i.e., self-reported). Participants are informed about this by the information letter and informed consent form. As a starting point, 4 patients in each group (i.e., adherent and non-adherent) will be interviewed. New interviews will be done until saturation is reached.

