### Statistical analysis

#### Primary analyses

Significant differences at baseline between the conditions will be checked by performing one-way ANOVA’s and chi-square tests.

Effects of the intervention on all outcomes will be assessed by performing intention-to-treat analyses using general linear mixed models. Baseline to post-intervention and 3- and 6-month follow-up differences will be used as repeated measures, with treatment (2 levels), time (3 levels) and their first-order interactions as fixed factors. Confidence intervals of 95% will be calculated for all outcomes. Drop-out and non-adherence are relatively common in online interventions [56]. Therefore, secondary analyses will be performed to examine effects on outcome variables for participants who adhered to the intervention (i.e., all session completed and self-reported minimum of 2 h per week spent on intervention). At post-intervention and follow-up, effect sizes (Cohen’s *d*) will be calculated using means and standard deviations. Effect sizes of 0.80 are considered large, effect sizes of 0.50 are evaluated as moderate, and effect sizes of 0.20 are considered small [57].

Initiative on Methods, Measurement, and Pain Assessment in Clinical Trials (IMMPACT) recommendations will be followed to evaluate the proportion of participants showing clinically significant change [58]. Clinical improvement will be assessed with missing values imputed by the Expectation Maximization-algorithm. Proportions of clinically improved participants and Chi-square tests will assess statistically significant differences in the proportions for the two conditions. It will be calculated for (a) pain interference (MPI – Interference), (b) pain intensity (NRS), and (c) CIPN symptom severity (EORTC QLQ – CIPN 20). A decrease of at least 0.6 standard deviation will be assessed as evidence of clinically significant change for the MPI – Interference scale, based on the IMMPACT guidelines [58]. Decreases of 20% or higher in pain intensity (NRS) will be assessed as minimum and moderate changes. No specific IMMPACT guidelines exist for the HADS. Therefore, a distribution-based decrease of at least 1 standard error of the mean is recommended [58].

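### The secondary analysis of adherers is not protected by randomisation: adherence is self-selected after allocation and the waiting list cannot meet it before T4

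*Protocol article*

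**What the plan says.** All places are in the protocol article.

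- **Primary analyses, main model:** "Effects of the intervention on all outcomes will be assessed by performing intention-to-treat analyses using general linear mixed models", "with treatment (2 levels), time (3 levels) and their first-order interactions as fixed factors".
- **Primary analyses, adherers:** the article notes that "Drop-out and non-adherence are relatively common in online interventions" and for that reason adds that "secondary analyses will be performed to examine effects on outcome variables for participants who adhered to the intervention". The criterion is "all session completed and self-reported minimum of 2 h per week spent on intervention".
- **Other outcomes:** the same definition is used to choose interviewees. Session completion comes from the platform log: "Patients adhered to the intervention if all sessions were completed (i.e., based on data retrieved from Karify". The weekly hours are self-reported.
- **Waiting list condition:** "At 5 months after start (i.e., T4) participants in the WLC receive the opportunity to follow the intervention", and this access is unguided.
- **Process outcomes:** the platform records when each session was finished, so completion is available for every participant with access.

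The text on adherers names no comparator, no adjustment and no causal method. It does not say that the result is non-randomised.

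**The concern.** Randomisation makes the two arms comparable as wholes. It does not make the part of the ACT arm that finishes comparable with the whole WLC. People who complete six modules and report enough weekly hours may differ from those who stop in motivation, symptom course or life circumstances, and so in how their pain interference would have changed without the course. The WLC contains both kinds of people. Before T4 nobody there can show which kind they are, so no matching subset can be drawn.

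The stake is interpretation. The article expects 30% drop-out and calls non-adherence common, so the set-aside part of the ACT arm may be large. The analysis covers outcome variables in general. A null intention-to-treat result could therefore be followed by apparently positive adherer results, and a reader might take those as the effect of the course when it is used as intended.

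**Working it through.** **Possible comparators.** The article does not name one, so each reading is taken in turn.

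1. *ACT adherers against the whole WLC.* This is the natural reading, because the model has a two-level treatment factor. A selected group meets an unselected one.
2. *Change from baseline within adherers.* There is no control, so natural course and regression to the mean after a pain-score entry threshold are mixed with any effect.
3. *ACT adherers against WLC adherers.* This is impossible at T3 and T4. At T5 it would compare two self-selected groups, one guided and one unguided, at different times since the course.

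None is protected by randomisation. The rest quantifies reading 1.

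**Plan's own figure.** The article states no figure for this analysis. From its sample size section I take only 73 randomised per group, 51 per group at follow-up (73 × 0.70 = 51.1) and d = 0.50.

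**Assumptions, not in the document.** p is the share of ACT that adheres, taken as 0.4 to 0.6. D is the gap between adherers and non-adherers in untreated change, taken as 0.2 to 0.5 SD, positive if adherers would do better anyway.

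**Bias.** With no treatment effect, the whole ACT arm has the same expected change as the WLC. Let the non-adherer mean be m and the adherer mean m + D. The arm mean is then m + pD, and

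bias = (m + D) − (m + pD) = (1 − p)D.

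**False-positive rate** for a two-sample comparison of 73p adherers with 51 WLC completers:

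SE = √(1/(73p) + 1/51), and rate = P(|Z + bias/SE| > 1.96).

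| p | adherers | SE | D | bias (SD) | bias/SE | rate |
|---|---|---|---|---|---|---|
| 0.4 | 29.2 | 0.232 | 0.2 | 0.12 | 0.52 | 8.1% |
| 0.4 | 29.2 | 0.232 | 0.5 | 0.30 | 1.29 | 25.3% |
| 0.5 | 36.5 | 0.217 | 0.2 | 0.10 | 0.46 | 7.5% |
| 0.5 | 36.5 | 0.217 | 0.5 | 0.25 | 1.15 | 21.1% |
| 0.6 | 43.8 | 0.206 | 0.2 | 0.08 | 0.39 | 6.7% |
| 0.6 | 43.8 | 0.206 | 0.5 | 0.20 | 0.97 | 16.3% |

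The bias is 0.08/0.50 = 16% to 0.30/0.50 = 60% of the effect the trial is sized for. At D = 0 the bias is zero and the rate is 5%. At negative D the table has the same rates, but the spurious effect runs against ACT.

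**Other group sizes.** The table counts adherers out of all 73 but the WLC as completers only. With 73 in the WLC, the SE is 0.191 to 0.219 and the rate 7.0% to 27.8%. With 51p adherers against 51, the SE is 0.229 to 0.262 and the rate 6.4% to 20.8%. The picture does not depend on that choice.

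**Second parameterisation.** In a simulation with no treatment effect (20,000 runs per setting), the top 30%, 50% or 70% of 73 ACT participants on a latent adherence propensity were kept. The propensity had correlation ρ with favourable outcome. They were compared with 73 or 51 unselected WLC participants by t-test. For ρ from 0.1 to 0.4 the bias was 0.05 to 0.46 SD and rejection about 5.5% to 47%. At ρ = 0 rejection was about 5%.

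**The case against.** - **The comparator is inferred.** This stands as a matter of text, and the bias figures apply to reading 1 only. It does not remove the point: the article commits to effects in adherers and fixes who they are, and no available comparator makes that a randomised contrast. This goes beyond a detail left to an analysis plan.
- **The analysis is secondary.** This stands. Intention-to-treat is the main analysis of every outcome, and its type I error is untouched. The label limits the damage but does not correct the adherer estimate.
- **Bias is conditional.** This stands in full. A reader might infer that the analysis must favour ACT and must inflate false positives. The document does not support that, because it gives neither the adherence share nor any link between adherence and prognosis.
- **The planned model uses change from baseline.** This stands in part. A stable difference in level between adherers and others is largely removed, so only a gap in untreated change matters, and D is defined that way here. The two-sample SE is still a simplification of a mixed model, so the rates are illustrative.
- **T5.** A reader might infer that the problem grows at T5, once the WLC has been offered the course. That is not shown. If the course works, WLC uptake would shrink the contrast, opposite to favourable selection, and it affects the intention-to-treat contrast at T5 too. T5 is better called uninterpretable for this purpose.

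**Conclusion.** The concern holds in a conditional form. The planned adherer analysis conditions on a self-selected, post-randomisation state that the WLC cannot reach before T4, so it does not give a randomised estimate of the effect among adherers. It can be biased in either direction, and is unbiased only if adherence is unrelated to untreated change.

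For p = 0.4 to 0.6 and D = 0.2 to 0.5 SD, the bias is 0.08 to 0.30 SD and the two-sided false-positive rate about 7% to 25%. Both inputs are assumptions, and the rates are for a simple two-sample comparison. The primary conclusion of the trial is not at risk. The secondary one should be changed before results are reported.

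**What to change.** 1. **At T3 and T4,** replace the adherers-only effect with a complier-average causal effect (CACE). Use the randomised arm as instrument and completion of all sessions from the Karify log (yes/no) as exposure, with baseline score, age and sex as covariates. WLC exposure is zero by design before T4. The self-reported hours are left out of the exposure, which then rests on logged data.
2. **Missing outcomes:** handle them as in the intention-to-treat analysis. Instrumental-variable estimation does not deal with the expected 30% drop-out by itself.
3. **State the exclusion restriction.** With the yes/no exposure it says that allocation to ACT does nothing for people who stop early. If partial users do gain, the estimate overstates the effect of completing.
4. **Sensitivity analysis:** use modules finished (0 to 6) as exposure. Report it as an average per-module effect, assuming roughly linear benefit. It is a different quantity from the effect in full adherers.
5. **Any adherers-only table:** label it descriptive and non-randomised, name its comparator, and omit p values and T5.

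**Cost.** A few sentences and one extra model with a sensitivity run, on data already collected. The interval is wider: for the yes/no exposure, the SE is about 1/p times the intention-to-treat SE. As a rough guide with 51 per arm, √(2/51) = 0.198 SD, so p = 0.6 gives 0.198/0.6 = 0.33 SD and p = 0.4 gives 0.198/0.4 = 0.50 SD. Baseline adjustment would reduce both.

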### Sample size calculation

Per group, 51 participants during follow-up measurements are necessary to detect minimal effect sizes of interest (*d* = .50) on the primary outcome. This is based on earlier findings on effectiveness of online and face-to-face ACT intervention for chronic pain [33, 34]. The power will be high enough (*p* = 1-beta = .80) to find significant effects in a two-sided test at alpha = .05. As found in previous online ACT interventions, a drop-out rate of 30% needs to be considered. G*Power calculations revealed that 73 participants per group are needed at baseline, which means that 146 participants are needed in total.

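### Responder rates come from EM-filled values and an ordinary chi-square: with 30% drop-out this can inflate the type I error or dilute the difference, depending on whether arm is in the EM model

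*Protocol article*

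**What the plan says.** All of this is in the protocol article, under Primary analyses and Sample size calculation.

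- Missing data for the responder analysis: "Clinical improvement will be assessed with missing values imputed by the Expectation Maximization-algorithm".
- Test: "Chi-square tests will assess statistically significant differences in the proportions for the two conditions".
- Outcomes: "It will be calculated for (a) pain interference (MPI – Interference), (b) pain intensity (NRS), and (c) CIPN symptom severity".
- Cut-off for the primary outcome: "A decrease of at least 0.6 standard deviation will be assessed as evidence of clinically significant change for the MPI – Interference scale".
- Expected loss: "a drop-out rate of 30% needs to be considered", which takes 51 per group at follow-up to 73 per group at baseline.

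For this step the article mentions neither multiple imputation nor a correction of the variance. It does not list the variables in the EM model or say whether treatment arm is among them. The main effect analysis is separate: "Effects of the intervention on all outcomes will be assessed by performing intention-to-treat analyses using general linear mixed models".

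**The concern.** Two features of the stated method work against each other. EM in its usual form replaces a missing score by its conditional mean. Such values vary less than real scores, so the share that crosses a cut-off differs from the true share. The chi-square then counts each filled-in participant as an independent observation, although all fills in an arm depend on the same estimated mean and slope. An error in that estimate moves all of them together.

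What happens next depends on a choice the article leaves open. With arm in the EM model, the shared error differs between arms and enters the contrast. Without arm, imputed participants in the two arms are treated alike and pull the contrast towards zero. At stake is the trial's statement on clinically significant change, including that for the primary outcome.

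**Working it through.** **Inputs.** From the article: 73 per group, 51 at follow-up, cut-off c = 0.6 SD, d = 0.50, two-sided alpha 0.05. Assumed, because not given: normal scores, baseline SD as the unit, correlation ρ between measurements, mean decrease μ, data missing completely at random, conditional-mean fill-in without residual noise.

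**Step 1, the plan's own figure.** 51/0.70 = 72.9, so 73 per group. The drop-out step reproduces. Imputed per arm: 73 − 51 = 22. Weights: 51/73 = 0.699 observed, 22/73 = 0.301 imputed.

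**Step 2, responder shares, imputing from baseline by arm.** A real decrease has mean μ and SD √(2(1−ρ)), so the true share is p = 1 − Φ((c−μ)/√(2(1−ρ))). An imputed decrease is μ + (1−ρ)z, with z the standardised baseline score, so the imputed share is q = 1 − Φ((c−μ)/(1−ρ)). The filled-in rate is 0.699p + 0.301q. At ρ = 0.7:

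| μ | true p | imputed q | filled-in rate |
|---|---|---|---|
| 0 | 0.219 | 0.023 | 0.160 |
| 0.3 | 0.349 | 0.159 | 0.292 |
| 0.6 | 0.500 | 0.500 | 0.500 |

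The rate is about 6 points too low at μ = 0 and 0.3, and unbiased at the cut-off.

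**Step 3, responder difference at d = 0.50** (ρ = 0.6, waiting list μ = 0, ACT μ = 0.5).

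- Truth: 0.455 − 0.251 = 0.204.
- EM without arm: both arms are imputed with μ = 0.25, so q = 0.191 in each and the imputed part contributes no difference. Result: 0.699 × 0.204 = 0.143, 30% smaller.
- EM by arm: q = 0.401 and 0.067. Filled-in rates are 0.439 and 0.196, difference 0.244, 19% larger.

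**Step 4, type I error by arm** (ρ = 0.7, both arms μ = 0.3). Variance of one filled-in proportion:

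- Observed part: 0.699² × 0.349 × 0.651/51 = 0.00218.
- Imputed part: 0.301² × 0.159 × 0.841/22 = 0.00055.
- Shared error of the estimated mean: its variance is (1−ρ²)/51 = 0.0100, and q changes by φ(1)/0.3 = 0.807 per SD. So 0.301² × 0.807² × 0.0100 = 0.00059.
- Covariance of that error with the observed share: 0.51 × 0.370/(0.775 × 51) = 0.00478. So 2 × 0.699 × 0.301 × 0.807 × 0.00478 = 0.00162.

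The sum is 0.00494. The chi-square assumes 0.292 × 0.708/73 = 0.00283. The ratio is 1.74, and the rejection rate is 2[1 − Φ(1.96/√1.74)] = 13.8%. This ignores error in the slope; simulation gives 15.0%.

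**Step 5, range by simulation.** 73 per arm, 30% missing, ρ = 0.5, 0.7 or 0.85, common mean decrease 0, 0.3, 0.5 or 0.6 SD, drop-out all after baseline or gradual over four time points: 24 null scenarios of 2,000 replicates each, uncorrected chi-square.

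| Method | Type I error | Above 10% |
|---|---|---|
| EM by arm | 5.8–30.6% | 20 of 24 |
| EM with arm as covariate | 5.4–27.1% | 17 of 24 |
| EM without arm | 4.1–6.0% | none |
| Observed cases only | 4.4–7.0% | none |

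The Monte Carlo standard error at 5% is √(0.05 × 0.95/2000) = 0.5 points. Observed cases stay near 5%, so the inflation comes from the imputation and not from the chi-square itself.

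At d = 0.50:

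- EM without arm, baseline only: 0.187 to 0.131 and 0.230 to 0.161 (30% smaller).
- EM without arm, four time points: 0.189 to 0.157 and 0.229 to 0.195 (15–17% smaller). The mildest scenarios lose 10–13%, for example 0.352 to 0.315.
- EM by arm: 0.250 to 0.336 (baseline only) or 0.311 (four time points). In one scenario (ρ = 0.85, baseline only, no change on the waiting list) it fell slightly, 0.291 to 0.283.

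**Step 6, the remedy.** Multiple imputation with 20 data sets, arm in the model and Rubin's rules: type I error 2.7–4.3% in six null scenarios (600 replicates each). The differences are 0.186 against 0.187 with full data, and 0.229 against 0.230.

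**The case against.** The strongest reply is that the size of the problem depends on things the article does not state, and that a condensed article may leave the content of the EM model to a fuller document. That is right about the size. A reader might infer that the type I error is more than doubled outright, but this does not follow. With no mean change under the null it is 5.8–13.1% by arm and 5.4–9.2% with arm as covariate. Without arm it is held.

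Two other strong readings also fail. It is tempting to say that nearly all imputed participants in an arm land on the same side of the cut-off. In Step 3 the imputed ACT group splits 40 to 60. Nor are responder rates always too low by a fixed amount: Step 2 shows the bias vanishing as the mean change approaches the cut-off. The 30% dilution is the unfavourable end, because it uses baseline only and the trial also measures at T1 and T2.

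It is also fair that the mixed models do not use EM and that the sample size was not set for responder proportions. A reader who inferred that the main effect estimate is compromised would be wrong.

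What remains is that the combination of EM fill-in and chi-square is stated, not left open. Under either choice about arm, the test or the estimate suffers. Adding residual noise to one filled-in data set would ease the bias in the rates, but the chi-square would still count 73 observed participants per arm.

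**Conclusion.** The point holds for the responder comparison. With arm in the EM model, the type I error can rise to roughly 6–30%, often above 10%, and the responder difference is mostly exaggerated. Without arm, the type I error is held but the difference is diluted by about 15–30%, somewhat less in the mildest scenarios. Responder rates themselves are biased unless the mean change lies near the cut-off.

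The ranges assume correlation 0.5–0.85, a common mean change of 0–0.6 SD, data missing completely at random, the planned 30% drop-out and no residual noise. The direction of each effect is well supported; a single figure is not. The matter should be corrected, but it does not touch the mixed-model analysis of the outcomes.

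**What to change.** In Primary analyses, replace the EM step by multiple imputation of the continuous scores, with treatment arm, baseline and the intermediate measurements in the model; 20 or more data sets would do. Derive responder status in each completed data set after imputation. Combine the responder difference and its test by Rubin's rules, in place of the chi-square on one filled-in data set.

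No new data are needed. The cost is slightly more analysis work and wider confidence intervals, which reflect the information lost to drop-out. In the simulations the corrected test was slightly conservative.

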### Randomization

When the patient is admitted to the study, the patient will receive confirmation of participation, the result of randomization, and the baseline questionnaire (T0b). Patients will be randomized to receive either ACT or WLC. The study will stratify by age and sex by means of block-wise randomization. An online generator will be used for this. Randomization will be performed by a research associate.

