#### Secondary analyses

To assess predictors of effects, steps of a study on predictors of change during CBT for chronic pain will be followed [59]. Pain interference at 3-month follow-up will be used as indicator of treatment effect. Using the PROCESS macro for SPSS [60], linear regression models will be applied (two-tailed). Predictor variables may include sex, age, educational level, number of comorbidities, time since CIPN onset, CIPN symptom severity (EORTC QLQ – CIPN20), quality of life (EORTC QLQ-C30), pain intensity (NRS), psychological distress (HADS), psychological inflexibility (PIPS), mindfulness (FMI-NL), valued based living (ELS), and pain catastrophizing (PCS). They will be selected based on theoretical and empirical considerations.

To assess differences in effects between the guided and unguided version of the intervention, independent samples t-tests and a two-stage hierarchical multiple regression analysis for each primary and secondary outcome will be conducted. Baseline to 3-month follow-up change will be used as the dependent variable. The independent variable will be an intervention dummy variable. Baseline score on the respective outcome measure will be used as control variable. Effect sizes for both conditions will be computed to indicate differences in the magnitude of the effects of online ACT with and without email counseling.

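### The responder comparison uses an unadjusted chi-square although the same-scale baseline score is collected; adjusting for it would add a modest amount of power for MPI Interference

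*Protocol article*

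**What the plan says.** Under Primary analyses, participants are classed as clinically improved on MPI Interference, pain intensity (NRS) and CIPN20, and "Chi-square tests will assess statistically significant differences in the proportions for the two conditions". No baseline score or stratification factor is attached to that test.

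The stated thresholds are changes from baseline. For MPI Interference, "A decrease of at least 0.6 standard deviation will be assessed as evidence of clinically significant change"; for the NRS, "Decreases of 20% or higher in pain intensity (NRS) will be assessed as minimum and moderate changes". No threshold is stated for CIPN20. Missing data are covered separately: "Clinical improvement will be assessed with missing values imputed by the Expectation Maximization-algorithm".

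Three other statements bear on the point:
- Randomization: "The study will stratify by age and sex by means of block-wise randomization".
- Main mixed model, also under Primary analyses: "treatment (2 levels), time (3 levels) and their first-order interactions as fixed factors". This is a separate analysis and does not adjust the responder test.
- Secondary analyses, guided versus unguided comparison: "Baseline score on the respective outcome measure will be used as control variable". The plan therefore already adjusts for baseline in another comparison.

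**The concern.** Defining response as a drop from baseline is not the same as adjusting for baseline. Because of regression to the mean, high scorers at entry tend to fall and low scorers tend not to, in both arms. Baseline therefore predicts response, and a two-by-two table leaves that information unused: a chance imbalance in baseline passes into the difference in proportions.

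What is at stake is power. The responder comparison starts from low power because a continuous score has been dichotomised, so a few points matter somewhat. The chi-square also gives a p-value but no adjusted size of difference.

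**Working it through.** **Inputs from the protocol article.** 51 per group at follow-up, 73 per group at baseline, 30% drop-out, two-sided alpha .05, and "minimal effect sizes of interest (*d* = .50) on the primary outcome" (Sample size calculation); MPI response = a drop of at least 0.6 SD (Primary analyses).

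**Assumptions, not in the document.** Normal scores; the SD in the 0.6 SD rule is the baseline SD; correlation r between baseline and follow-up of .4 to .8; no missing data.

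**The plan's own figure.** No power is given for the responder comparison. The only sample-size figure is for the primary outcome. Its drop-out step reproduces: 51/0.7 = 72.9, so 73 per group and 146 in total. The 51 does not: a two-sided t-test at d = .50 and 80% power needs 64 per group, while 51 is the one-sided answer (50.15, rounded up). That is a separate matter; 51 and 73 are used here only as the planned group sizes.

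**Step 1: is baseline prognostic for response?** With baseline b in SD units, an untreated participant responds with probability Φ(((1 − r)b − 0.6)/√(1 − r²)). At r = .6:
- b = −1: Φ(−1.0/0.8) = Φ(−1.25) = 11%
- b = +1: Φ(−0.2/0.8) = Φ(−0.25) = 40%

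**Step 2: chi-square power by formula.** The change score has SD s = √(2(1 − r)). Response rates are 1 − Φ(0.6/s) in the control arm and 1 − Φ((0.6 − 0.5)/s) in the ACT arm. At r = .6, s = 0.894 and the rates are .251 and .455. With 51 per group, the standard error is .0947 under the null (pooled) and .0925 under the alternative, so power = Φ((.2043 − 1.96 × .0947)/.0925) = Φ(0.20) = .58. Over r = .4 to .8 the formula gives .43 to .84 at 51 per group and .57 to .95 at 73.

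**Step 3: chi-square against logistic regression.** 2,000 simulated trials per row, likelihood-ratio test of arm, age and sex given no effect on outcome:

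| n per group | r | chi-square | + baseline | + baseline, age, sex | gain (points) |
|---|---|---|---|---|---|
| 51 | .4 | .438 | .519 | .530 | 9.2 |
| 51 | .5 | .496 | .564 | .568 | 7.2 |
| 51 | .6 | .586 | .640 | .646 | 6.0 |
| 51 | .7 | .711 | .746 | .750 | 3.9 |
| 51 | .8 | .851 | .868 | .872 | 2.1 |
| 73 | .4 | .582 | .670 | .676 | 9.4 |
| 73 | .5 | .650 | .724 | .729 | 7.9 |
| 73 | .6 | .744 | .805 | .808 | 6.4 |
| 73 | .7 | .828 | .873 | .876 | 4.8 |
| 73 | .8 | .943 | .957 | .959 | 1.6 |

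The simulated chi-square column agrees with Step 2. A separate simulation with baseline as the only covariate gave similar or slightly smaller gains: at 51 per group, .45 to .50 (r = .4), .60 to .63 (r = .6) and .84 to .86 (r = .8).

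**Step 4: where the gain comes from.** Stratifying on age and sex alone (Cochran-Mantel-Haenszel) changes power by less than 1 point. Adding age and sex to baseline gives 0 to 2 points, including when each shifts the outcome by 0.2 SD.

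**Step 5: NRS, 20% rule.** Further assumptions: baseline mean 5.5, SD 1.8, scores of 3 or more only. Adding baseline changes power at 51 per group from .530 to .553 (r = .4), .661 to .669 (r = .6) and .858 to .858 (r = .8). At 73 per group the gains are 2.8, 0.3 and 0.1 points.

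**Step 6: type I error, complete data.** At 73 per group and r = .5 and .7 (3,000 runs): chi-square .050 and .047; logistic with baseline, age and sex .055 and .048.

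**Step 7: type I error after imputation.** Assume 73 per group, 30% missing at random, and a single conditional-mean imputation from baseline and arm. Two separate simulations gave null rejection rates, chi-square then logistic, of .105 and .131, and of .096 and .111, at r = .4; and of .082 and .083, and of .080 and .087, at r = .6. With arm left out of the imputation model, both tests stay near .05.

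**The case against.** The strongest reply is that nothing here is an error. A chi-square is valid in a randomised comparison, it holds its level on complete data, and the responder analysis only supports a mixed model that covers all outcomes. Dichotomising costs far more than leaving out a covariate: at r = .5 and 51 per group, analysis of covariance on the continuous score has power .82 against .50 for the chi-square. All of that stands, and it keeps the point minor. It does not remove it: the document fixes the test by name, and a better one is available from data already collected.

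A reader might also infer four stronger points, none of which the document supports:
- **That all three responder endpoints lose this much.** The 2 to 10 points belong to the MPI rule. The NRS gain is 0 to 3 points, and without a CIPN20 threshold no loss can be calculated there.
- **That ignoring the randomisation strata causes the loss.** Step 4 shows that it contributes almost nothing. Age and sex belong in the model only because randomisation was stratified on them.
- **That the benefit holds however missing responders are imputed.** Step 7 shows that with arm in a single imputation model neither test need hold 5%, and the adjusted test can be somewhat worse. The inflation comes mainly from the imputation. The 73-per-group powers are complete-data figures, whereas the plan expects about 30% of those values to be imputed.
- **That responder rates carry the trial's claim of clinical benefit.** The document does not say so.

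**Conclusion.** The point holds as a minor matter of efficiency: a valid but avoidably weak test for the MPI responder comparison. The size rests on the assumed correlation, for which the document gives no value, and on a true effect of .50 SD with complete data. If the correlation is as high as .8, only about 2 points are at stake. The case for changing is that the covariate is prognostic, already collected and already used as a control variable elsewhere in the plan. The protocol does not give a wrong result by using the chi-square.

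**What to change.** Replace the chi-square with a logistic regression of responder status on arm, the continuous baseline score of the same scale, age and sex, testing the arm term. From that model report the standardised (marginal) difference in responder proportions with its 95% interval, so that the quantity remains a difference in proportions and not a conditional odds ratio. Keep the crude proportions by arm as description.

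The cost is one sentence in the plan and slightly more analysis work; no new data or participants are needed. The change does not deal with the understated uncertainty from single Expectation Maximization imputation, which affects either test and has to be settled separately.
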